## Background

As of June 2015, there have been 1,667 Service Members with combat related amputations treated at the three major United States Military Treatment Centers since the start of Operation Iraqi Freedom (OIF), and into Operation Enduring Freedom (OEF) and Operation New Dawn (OND) (1). More than half of these Service Members are now Veterans, and 95% of OEF/OIF/OND Veterans with limb loss use the VA Healthcare System within 5 years of separation from active duty (2). VA now has a responsibility to serve this unique population for their lifetime, as well as provide care to an additional 40,000 Veterans that have lower extremity limb loss at levels proximal to the ankle (3). For those receiving prosthetic foot-ankle devices, the providers within the amputation care team have well over 100 choices of commercially available prosthetic feet to prescribe (4). In the constantly evolving climate of prosthetic devices, there are limited guidelines available to aid clinicians in prescribing the appropriate components, which is a critical unmet need in the field of prosthetics in the VA and military healthcare systems (5).

The standard of care of VA and DoD amputation care teams, supported by the available literature and clinical consensus, is to prescribe Energy Storing and Returning (ESR) feet (Figure 1) to Veterans and Service Members regardless of guidelines established by Centers for Medicare & Medicaid Services (CMS). This means that ESR ankle-foot units, which kinetically and kinematically out perform traditional options such as the Solid Ankle Cushion Heel (SACH) and Stationary Attachment Flexible Endoskeletal (SAFE) feet (6), are recommended and/or prescribed to all Veterans and Service Members that are ambulatory. This broad clinical decision making is supported by Nielson et al, whose findings on the first ESR ankle-foot unit, the “Flex-Foot”, demonstrated significant improvement in walking speed and a reduction in the energy cost of ambulation over traditional prosthetic foot options (6). ESR feet have also been shown to improve stair ascent initiation by reducing the time of initial double-limb support (7), reducing the requisite activation for propulsive muscles (8), and, as the name would indicate, improving elastic response (9). VA and Military healthcare systems affiliated with this proposal have adopted this current standard of clinical practice, but concur there is insufficient evidence to support prescription of specific prosthetic feet within the overarching classification of ESR ankle-foot devices (10-12).

[figure not shown]

Figure 1. Common examples of the over 100 commercially available ESR feet

There are less commonly prescribed, more advanced ESR options commercially available, including articulating ankles that can present as a passive hydraulic, microprocessor-controlled, or powered units (Figure 2). Articulating ankles in prosthetic feet have been traditionally thought to decrease energy return for individuals with transtibial amputation (TTA), but recent evidence on current articulating ESR ankle-foot units (i.e. Endolite Echelon, Fillauer Motion Foot, Freedom Innovations Kinterra, Otto Bock Triton Smart Ankle, Ossur Proflex) and microprocessor controlled ESR ankle-foot units (i.e. Endolite Elan, Ossur Propriofoot, Hosmer Raize), suggest that articulating hydraulic and microprocessor-controlled non-powered ankle-foot units can improve ambulation on level ground as well as on inclines and stairs (10). De Asha et al. described improved progression of the center of pressure in a prosthetic foot with a hydraulic ankle unit in a population of individuals with TTA and transfemoral amputation (TFA) (13), and Portnoy et al. found a decreased load at heel strike when using an ESR hydraulic ankle-foot unit (14). Fradet et al. reported that a microprocessor controlled ankle improved kinematics in ramp ascent and made patients feel safer during ramp descent (15). This evidence suggests that Veterans and Service Members with TTA that negotiate specific environments may benefit from an articulating ankle ESR foot over a fixed-ankle ESR foot.

[figure not shown]

Figure 2. Articulating ankle ESR feet, clockwise from top left Propriofoot, Echelon, Kinterra,

Commercially available ESR feet with active (i.e. powered) plantarflexion (i.e. iWalk BiOM) have potential biomechanical benefits to the user beyond that of the ESR or articulating ankle ESR options (Figure 3). The iWalk BiOM (Bedford, MA) works to replicate the dynamic contractile tissues of the gastroc-soleus complex for individuals with a lower extremity amputation (16). This biomimetic prosthetic device has the ability to normalize ankle power, potentially reducing kinetic asymmetries that lead to musculoskeletal

imbalances, thus improving physical function (16). Grabowski and D'Andrea noted that individuals with TTA using the BiOM had a reduction in peak resultant force and knee adduction moment on the unaffected leg during level-ground walking, potentially limiting the risk of secondary musculoskeletal comorbidities which are common in this population (11, 17-20).

Despite the noted advances in prosthetic technology, much of the research efforts and clinical practice have focused on the design and function of prosthetic technology, rather than understanding which devices are most appropriate to prescribe for individuals with lower limb amputation. Prescription of specific ankle-foot units within VA and DoD healthcare systems, as well as the private sector, is often based on anecdotal evidence or manufacturer driven research (21-23). Furthermore, limitations in the research studies conducted to date, including small sample sizes and non-standardization of feet, make it difficult to directly apply scientific evidence to clinical decision making. This proposal will fill this critical unmet need. Through a multi-centered clinical trial (n =120), the standardization of prosthetic foot characteristics, and matching real-world testing environments, we believe we will be able to come to statistically significant results to determine which patient goals and outcome measures are most indicative in yielding the most successful and appropriate ankle-foot prosthesis prescription. As such, this study will use step activity monitors, a battery of physical and subjective functional outcome measures, along with biomechanical kinetic and kinematic data to facilitate evidenced-based practice that will be used for a lifetime of care delivery to our Veterans and Service Members living with TTA. This will be addressed through a four center investigation capturing 120 participants with TTA, which will be largest study of this kind ever conducted. The distribution of sites include VA and DoD covering various geographical and demographical locations.

[figure not shown]

Figure 3. ESR foot with powered plantarflexion

#### **Preliminary Data: A Controlled, Longitudinal Evaluation of the iWalk BiOM (PI: [name])**

VA New York Harbor Healthcare System (VANYHHS) is currently conducting a 12-month longitudinal investigation of the BiOM in individuals living with TTA. The primary objective of the investigation is to clinically test and quantitatively evaluate the biomechanical efficacy, functional performance, and daily use of individuals with TTA utilizing the BiOM for 12-months through kinematic and kinetic analysis, functional measures, and step activity monitoring, respectively, many of the same measures that will be collected for this proposal. Figure 4 shows that after 6 months of BiOM use, kinetic asymmetries of the sagittal plane hip kinetics at day 30 have resolved (Figure 3 C&F). Both the sagittal plane hip moment and power have become symmetrical to the intact side, suggesting that the increased power of the prosthetic ankle has reduced the need for hip compensatory strategies.

[figure not shown]

Figure 4: Sagittal plane hip plane moments (A-C) and powers (D-F) for a representative subject at days 30, 90 and 180. Red lines represent the means for the BiOM limb. Blue lines represent the means for the intact limb.

Functional measures also generally improved while utilizing the BiOM. Figure 5 details the results of the 6-minute walk test (6-min walk) (Fig 5A), the four square step test (4SST) (Fig 5B), and the Timed-Up-and-Go (TUG) (Fig 5C) for all enrolled subjects at baseline (ESR foot), as well as after 30 and 180 days of BiOM use. Results show improvements in the 6-min walk distance and speed using the BiOM compared to the ESR foot, while average TUG times did not change

from the baseline condition. The BiOM does not provide an assist during lateral or backward movement, and is heavier than a non-articulating ESR foot. As such, it was expected BiOM use to produce slower 4SST times. However, average 4SST times

[figure not shown]

have exhibited a decrease in 4SST time while utilizing the BiOM. Anecdotally we have also found an approximate 50% user rejection rate of the BiOM despite the functional and biomechanical improvements measured, suggesting that prosthetic prescription guidelines for the BiOM may need to be further refined to determine which patients may not only benefit from the technology, but also accept it.

### Objectives / Specific Aims / Hypotheses

The purpose of this study is to develop criteria for prosthetic foot prescription for Veterans and Service Members with transtibial limb loss. The objectives are as follows:

- Determine the appropriate functional outcome tests and measures to support the prescription of a type of ESR (non-articulating, articulating or active plantarflexion) prosthetic ankle-foot for a Veteran or Service Member with transtibial limb loss.
- Correlate patient goals and subjective measures with objective data to determine the appropriate prosthetic ankle-foot category that will facilitate the greatest overall function to the user.
- Develop criteria for the appropriate prescription of non-articulating ESR, articulating ESR, and active plantar flexion ESR ankle-foot units.

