### Specific Aim 1 – To evaluate the differences in functional performance and subjective outcomes between non-articulating ESR, articulating ESR, and active plantarflexion ESR feet.

Hypothesis 1.1 Subjects will demonstrate improvement and preference for articulating ESR and active plantar flexion ESR feet over the non-articulating ESR feet for community mobility, particularly for those that regularly negotiate inclines and declines.

Hypothesis 1.2 Active plantar-flexion ESR feet will result in better performance metrics for mobility based outcome measures.

Hypothesis 1.3 Subjects will have decreased low back and proximal joint pain scores as determined by the visual analog scale within the Prosthetic Evaluation Questionnaire (PEQ) when using the active plantarflexion ESR foot.

Hypothesis 1.4 There will be no significant differences in functional outcome measures within all tested non-articulating ESR feet regardless of specific foot assigned.

Hypothesis 1.5 There will be no significant differences in functional outcomes within all articulating ESR feet tested regardless of specific foot assigned.

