### Specific Aim 2– To evaluate the kinematic and kinetic differences of non-articulating ESR, articulating ESR, and active plantar flexion ESR feet in individuals with transtibial amputation

Hypothesis 2.1 Plantarflexion forces (i.e. ground reaction forces) at push off /terminal stance will be most symmetrical to the intact limb for active plantarflexion devices, followed by non-articulating ESR feet, and lastly articulating ESR devices.

Hypothesis 2.2 Biomechanical symmetry in gait while negotiating a decline will be greater for both active plantarflexion ESR and articulating ankle ESR conditions compared to non-articulating ESR feet.

Hypothesis 2.3 Biomechanical symmetry in gait while negotiating an incline will be greatest for devices with active plantarflexion, followed by articulating devices, and lastly non-articulating ESR feet.

Hypothesis 2.4 Ambulation at a faster than self-selected walking speed will yield decreased symmetry in articulating ankle ESR and non-articulating ESR feet but not with the active plantar flexion ESR feet.

Hypothesis 2.5 Articulating ESR feet will not yield significant differences in gait symmetry regardless of specific foot assigned within the articulating ESR category.

**Specific Aim 3 – To correlate biomechanical findings with functional and subjective outcome measures and with user preference determined through activity monitoring and user satisfaction to develop guidelines for appropriate prosthetic prescription.**

Hypothesis 3.1 Individuals that commonly negotiate ramps, hills, inclines or declines will show preference for an articulating ankle ESR and/or active plantarflexion ESR feet over non-articulating ESR feet

Hypothesis 3.2 Individuals that have higher step counts, but do so at a low activity level will prefer the active plantarflexion ESR ankle-foot prosthesis.

Hypothesis 3.3 The majority of subjects will chose to utilize a single prosthesis for all activities, and not use different prostheses for different activities, as measured through step activity monitoring and daily activity logs.

Hypothesis 3.4 Step activity performance will, and age will not, correlate with prosthetic feet category that best optimizes function.

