The end point of this study is to generate findings that offer new knowledge that can be developed into clinical practice guidelines, and/or new prescription algorithms for prosthetic ankle-foot units. This information will lead to clinical prescriptions that facilitate achievement of maximal functional ability. Plainly stated, criteria will be created to assist the amputation care team in prescribing appropriate advanced prosthetic ankle-foot systems based on specific patient needs, specific patient goals, in addition to the individual current physical abilities.

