## **Part 1a: Screening, Consent, Enrollment, Prosthetic Socket Assessment**

During the first visit, subjects will be screened according to the inclusion/exclusion criteria, consented and enrolled. Demographic information will be collected including, age, height, weight, injury etiology, and time as a prosthesis user. Fit and comfort of each subject's existing socket will be evaluated by the study prosthetist on-site through standardized prosthetic guidelines. Once fit and comfort are confirmed, the study prosthetist will create a mold using plaster of paris or alginate for fabrication of two identical prosthetic sockets.

Between visits 1 and 2, the molds of the existing socket shape and volume will be used to create laminated, definitive sockets, for the two additional prostheses. These sockets will be centrally fabricated at VANYHHS. The same materials as used in the subject's current socket will be used to create each additional socket to eliminate any variance in perceived weight or socket flexibility. Each additional socket will be aligned/programmed with a designated prosthetic foot to manufacturer's specifications by the study prosthetist.

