#### SA3 Data Analysis:

Daily step counts and level of activity (low, medium, high) will be collected from each SAM attached to each prosthesis, and daily activity logs will be analyzed to determine which devices were used for specific activities (i.e. everyday use, leisure, housework). Together, this will help determine rationale for patient preference of prosthesis. Additionally these findings will be correlated with previous outcome measures from Parts 2-4.

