#### Development of Prediction Model:

In order to develop guidelines for prosthetic prescription of ankle-foot devices, the goal of this proposal is to determine which factors and outcomes are most predictive of optimal performance to meet patient goals. To do this, initial analyses will consist of bivariate cross-tabulations, conducted using chi square analyses, based on clinical hypotheses between each potential explanatory variable. Variable selection for the multivariate model will be informed by bivariate findings. Logistic regression will then be performed with patient preference of prosthesis regressed on each of several domains (i.e. functional levels/outcomes, Activity levels, biomechanical parameters, among others). The models will control for multiple variables simultaneously. The C-statistic corresponding to the area under the receiver operating characteristic (ROC) curve will be used to assess overall predictive value. Theory-driven domain specific models (based on bivariate findings) and one parsimonious stepwise logistic regression model combining the domains will be created. This will help determine whether each distinct component predicts optimal prosthetic prescription outcome. Each domain-specific model will be adjusted for and controlled for confounding factors. The individual variables expressing the components of each domain will be entered as fixed predictors. Finally, a stepwise multiple regression will be applied to identify the set of clinical factors that represent the strongest independent predictors. The stepwise regression will be conducted through a series of domain-specific forward-regression models and one backward regression. The variables significant in these forward selection models will be placed in the backward model and will be removed at  $P = .10$ . The significant variables from the backward regression will be presented as the strongest independent predictive factors and be used to help guide prosthetic prescription.

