#### Power Analysis:

| Site                                                | n   | n for subset |
|-----------------------------------------------------|------------|---------------------|
| VA New York Harbor Healthcare System (NYC)          | 30         | 15                  |
| Walter Reed National Military Medical Center (D.C.) | 30         | 15                  |
| VA Puget Sound Healthcare System (Seattle)          | 30         | 0                   |
| James J. Peters VA Medical Center (Tampa)           | 30         | 0                   |
| TOTAL                                        | 120 | 30           |

Figure 7. Total Subjects per site to be seen over the course of 3 year period

#### Specific Aim 1

Functional measures will be analyzed by multilevel (site) repeated measures analysis of variance. Because order of prosthesis will be randomized, there should be no order effect. However, order will be included in the initial analysis to test this assumption. Assuming an alpha error rate of 5% and within-group standard deviation of 5, 120 subjects will provide over 98% power to detect a 3 unit difference between at least two of the ESR groups for each of the functional measures.

### Specific Aim 2

Kinematic and kinetic measures will be analyzed by multilevel (site) repeated measures analysis of variance. Because order of prosthesis will be randomized, there should be no order effect. However, order will be included in the initial analysis to test this assumption. Assuming an alpha error rate of 5% and within-group standard deviation of 10, 30 subjects will provide 72% power to detect a 6-unit difference between at least two of the ESR groups for each of the measures.

### Specific Aim 3

This analysis will be performed using paired t-test to determine correlations between prosthesis chosen as per SAM data and which functional outcome measures are indicative of that choice. Additionally pair t-test will be performed between kinematic and kinetic data to again correlate with the prosthetic choice of the subject as demonstrated through the SAM data. Finally all SAM data will be evaluated against the activity journal to determine the roll of a specific activity goal and a specific prosthesis.

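### Patient goals and habitual incline use are key predictors, but no section shown records either before a study foot is used, and the only stated source for goals overlaps the preference outcome

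*Protocol*

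**What the plan says.** **Where goals are needed.** Objective 2 is to "Correlate patient goals and subjective measures with objective data to determine the appropriate prosthetic ankle-foot category". The end-point paragraph after the Specific Aim 3 hypotheses promises prescribing criteria "based on specific patient needs, specific patient goals". The section Development of Prediction Model says that "the goal of this proposal is to determine which factors and outcomes are most predictive of optimal performance to meet patient goals".

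**Where incline use is needed.** Hypothesis 1.1 expects a preference for articulating and powered feet, "particularly for those that regularly negotiate inclines and declines". Hypothesis 3.1 reads: "Individuals that commonly negotiate ramps, hills, inclines or declines will show preference for an articulating ankle ESR" and/or a powered foot.

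**What is recorded at entry.** Part 1a: "Demographic information will be collected including, age, height, weight, injury etiology, and time as a prosthesis user".

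**What is recorded later.** The functional tests and the PEQ, SF-12 and OPUS are given after each one-week acclimation in Parts 2 to 4 (Outcome Measures). In Part 5 the subject has all three limbs for 30 days, keeps an activity log, and preference is defined by total activity time on each prosthesis. SA3 Data Analysis says that "daily activity logs will be analyzed to determine which devices were used for specific activities (i.e. everyday use, leisure, housework", where the bracket closes. Power Analysis, Specific Aim 3, says that "all SAM data will be evaluated against the activity journal to determine the roll of a specific activity goal and a specific prosthesis".

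**The concern.** Prescribing criteria are applied before a foot is supplied, using what is known about the patient at that moment. A predictor in such criteria has to be measured before the patient has used the devices being compared. Here the plan ties the activity goal to a journal kept while the subject is already choosing among three feet, and it names no source for habitual incline use.

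If activity in Part 5 stands in for the goal or the habit, cause and effect can run either way. A subject who takes to an articulating foot and therefore walks more hills would look like a hill walker who prefers that foot. A subject whose goal was hills but who did not get on with the foot could look like someone with no interest in hills. The study's main product, guidance on which patient should get which foot, depends on telling these apart.

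**Working it through.** No stated power or sample-size figure is at issue, so the check is mainly of what is recorded and when.

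1. **Before any study foot.** Part 1a lists demographics and a socket assessment. The inclusion criteria add the three FIM mobility items. The randomization section uses an activity-level rating on manufacturer parameters to select the foot. None of these is a goal or a measure of how often inclines are met.
2. **Parts 2 to 4.** No instrument is described as recording goals or frequency of incline use. The Hill Assessment Index rates how a subject manages an incline. The PEQ has an importance item group and mobility questions, which are possible partial proxies. They come after acclimation, and Part 1b has subjects fitted and trained on the study feet before Part 2 starts.
3. **Part 5.** The journal (source of the activity goal) and the step monitors (source of preference) cover the same 30 days. Predictor and outcome are not separated in time.
4. **Hypothesis 1.1.** The analysis section takes preference from the PEQ mobility questions in Parts 2 to 4. A Part 5 log would therefore record the moderator after the outcome and after use of all three feet.
5. **Two alternatives for incline use.** If the log does not capture terrain, the incline comparisons have no predictor. If it does, the predictor can be shaped by the foot. Only one of these can apply, and the text does not say which.

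**Illustration of the second alternative (all inputs assumed; none is in the protocol except n = 120).** Suppose there is no true link between habitual hill walking and preference, and a share h = 0.5 of subjects are true hill walkers. Among non-hill walkers who choose an articulating or powered foot, a share s log hills because of the foot.

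- Choosers classed as hill walkers: p = h + (1 − h)s. Non-choosers: h.
- Odds ratio = [p/(1 − p)] / [h/(1 − h)].
- s = 0: p = 0.50, OR = 1.0.
- s = 0.2: p = 0.5 + 0.5 × 0.2 = 0.60, OR = (0.60/0.40)/(0.50/0.50) = 1.5.
- s = 0.4: p = 0.70, OR = (0.70/0.30)/1 = 2.33.

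The same idea on a continuous scale: logged incline use is shifted by d standard deviations in those who prefer such a foot, and is tested by a two-sided two-sample t-test at 5% with 118 degrees of freedom and noncentrality d/√(1/n₁ + 1/n₂). Splits run from 40/80 to 60/60. The false-positive rate is 5.0% at d = 0, 17.6 to 19.2% at d = 0.2, 33.6 to 37.1% at d = 0.3, and 72.6 to 77.5% at d = 0.5. A record made before any study foot is used corresponds to d = 0.

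**The case against.** The strongest reply is that silence is not proof of absence. The Part 1a list is worded as open, the Figure 6 timeline is not shown, the text refers to an Intervention Plan that is not a section of the supplied document, and the log form is not shown. The three log categories may be examples only: the prediction-model section uses the same abbreviation before a list that ends by allowing others. Subjects are asked to document daily activities, which could include hills. A reader might infer that all 120 subjects lack a pre-exposure value, or that the log cannot separate inclines from level ground. The documents do not establish either. What stands is that variables this central are not specified at entry in any text shown, and that the one stated source for an activity goal is the Part 5 journal.

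Second, the non-articulating foot will typically be the subject's own (Foot Selection), so one PEQ is usually completed on a familiar device. That is a real mitigation, but a partial one: the order is random, so another study foot will often have come first, and the PEQ is not described as recording goals or terrain.

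Third, terrain may be fixed by home and work, in which case the foot changes little and the bias is near zero. That is possible. The Background, however, reports that articulating units can improve walking on inclines and that a microprocessor-controlled ankle made users feel safer on ramp descent, so an effect on where people walk is plausible on the protocol's own rationale.

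Finally, this cannot be left to an analysis plan, because data not collected before exposure cannot be analyzed later.

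**Conclusion.** The point holds in a limited form. As written, the goals part of Objective 2 and the incline comparisons in Hypotheses 1.1 and 3.1 are either unmeasured or, if taken from the Part 5 log, open to reverse causation of unknown size. This rests on the text shown and would fall away if an entry form not shown already records both items.

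Two stronger readings are not supported. A reader might infer that Hypothesis 3.1 is biased toward confirmation; but no section says that incline users are classified from the log, and the bias would need a log that registers hills, which is not shown. A reader might also infer that Objective 2 cannot be answered; but it covers subjective measures too, and those are collected three times. The odds ratios and false-positive rates above show a mechanism under assumed inputs and are not estimates for this trial.

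**What to change.** At visit 1, before feet are assigned, add a one-page form with (a) the subject's main mobility goals, ranked from a fixed list, and (b) usual weekly exposure to ramps, hills and stairs in fixed categories. Name these answers in the protocol as the goal and incline predictors for Objective 2, Hypotheses 1.1 and 3.1, and the prediction model. Add an incline/decline line to the Part 5 log, and use the log only to describe which foot was worn for which activity. If an existing entry form already records these items, cite it and state this use.

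The cost is a few minutes per subject at an existing visit and one extra line in the log, with no new visit or staff. It should be in place before subjects start on study feet, because later recall would itself be post-exposure.
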